### **3.10 Expected outcome**

This study is to be expected at the end of study, there will be an improvement in the level of foot self-care behaviour. The secondary outcome would be an improvement in efficacy expectation, outcome expectation, knowledge on foot care and quality of life of elderly with diabetes in Rumah Seri Kenangan. The information from the findings of this study may contribute as baseline information for the ministry concern. It is hope that in future, the programs among elderly especially in institutional care can helps to increase their health status towards healthy aging.

### **3.11 Summary**

In summary, this chapter has provided in detail of the research design, setting, population, sampling, sample size, construction of the intervention program and the questionnaire as a research tool, validity and reliability, data collection process, ethical approval, statistical analysis, pilot study and expected outcome. The next chapter will provide the data analysis of study.

## Appendix 1: Work plan

### Work plan

Effects of self-efficacy enhancing program on foot self-care behaviour of elderly with diabetes in Rumah Seri Kenangan, Peninsular Malaysia

| Gantt Chart |                                               | Year 1 |     |     |     |      |     |     |     |     |     |     |     | Year 2 |     |     |     |     |     |     |     |     |     |     |     |
|-------------|-----------------------------------------------|--------|-----|-----|-----|------|-----|-----|-----|-----|-----|-----|-----|--------|-----|-----|-----|-----|-----|-----|-----|-----|-----|-----|-----|
|             |                                               | 2014   |     |     |     | 2015 |     |     |     |     |     |     |     | 2016   |     |     |     |     |     |     |     |     |     |     |     |
|             |                                               | Sept   | Oct | Nov | Dec | Jan  | Feb | Mar | Apr | May | Jun | Jul | Aug | Sept   | Oct | Nov | Dec | Jan | Feb | Mar | Apr | May | Jun | Jul | Aug |
| 1           | Literature review                             |        |     |     |     |      |     |     |     |     |     |     |     |        |     |     |     |     |     |     |     |     |     |     |     |
| 2           | Proposal development                          |        |     |     |     |      |     |     |     |     |     |     |     |        |     |     |     |     |     |     |     |     |     |     |     |
| 3           | Seminar proposal and ethical approval process |        |     |     |     |      |     |     |     |     |     |     |     |        |     |     |     |     |     |     |     |     |     |     |     |
| 4           | Pilot study / material preparation            |        |     |     |     |      |     |     |     |     |     |     |     |        |     |     |     |     |     |     |     |     |     |     |     |
| 5           | Data collection / intervention process        |        |     |     |     |      |     |     |     |     |     |     |     |        |     |     |     |     |     |     |     |     |     |     |     |
| 6           | Data analysis and statistical conclusion      |        |     |     |     |      |     |     |     |     |     |     |     |        |     |     |     |     |     |     |     |     |     |     |     |

| Gantt Chart |                                 | Year 3 |     |     |     |      |     |     |     |     |     |     |     |
|-------------|---------------------------------|--------|-----|-----|-----|------|-----|-----|-----|-----|-----|-----|-----|
|             |                                 | 2016   |     |     |     | 2017 |     |     |     |     |     |     |     |
|             |                                 | Sept   | Oct | Nov | Dec | Jan  | Feb | Mar | Apr | May | Jun | Jul | Aug |
| 8           | Discussion/ implication         |        |     |     |     |      |     |     |     |     |     |     |     |
| 9           | Documentation and dissemination |        |     |     |     |      |     |     |     |     |     |     |     |

### Part A: Demographic data

Please **choose** the appropriate answer to each question and tick ( ☐ ) in the box provided and give answers where specified.

- Age : \_\_\_\_\_ years \_\_\_\_\_ months
- Gender : ( ☐ )1 Male ( ☐ )2 Female
- Ethnic : ( ☐ )1 Malay ( ☐ )2 Chinese  
( ☐ )3 Indian ( ☐ )4 Others
- Education level : ( ☐ )1 Never ( ☐ )2 Primary  
( ☐ )3 Secondary ( ☐ )4 Tertiary
- Marital status : ( ☐ )1 Never ( ☐ )2 Married  
( ☐ )3 Widowed ( ☐ )4 Separated
- No of children : \_\_\_\_\_
- Duration stayed at this RSK: \_\_\_\_\_ years \_\_\_\_\_ months

### Part B: Clinical characteristics

Please **choose** the appropriate answer to each question and tick ( ☐ ) in the box provided and give answers where specified. You may tick ( ☐ ) more than one answer

- Duration of diabetes : \_\_\_\_\_ years \_\_\_\_\_ months
- Treatment of diabetes : ( ☐ )1 Diet control ( ☐ )2 Oral medication  
( ☐ )3 Insulin ( ☐ )4 Others, \_\_\_\_\_
- Other disease (except diabetes) : ( ☐ )1No  
( ☐ )2Yes, \_\_\_\_\_
- Received diabetes education : ( ☐ )1No or  
**if yes**, the education is about \_\_\_\_\_, when: \_\_\_\_\_ from:  
nurse/ doctor/ or \_\_\_\_\_
- Current smoking : ( ☐ )1No ( ☐ )2Yes, \_\_\_\_\_
- Recent hospitalization : ( ☐ )1No ( ☐ )2Yes, \_\_\_\_\_

## Part C: Foot self-care behaviour

Section 1: The questions below ask you about your diabetes self-care activities during the past 7 days. If you were sick during the past 7 days, please think back to the last 7 days that you were not sick. Please circle in an appropriate answer.

|                                                 | The activities during the past 7 days |   |   |   |   |   |   |   |
|-------------------------------------------------|---------------------------------------|---|---|---|---|---|---|---|
| 1. I examine my feet                            | 0                                     | 1 | 2 | 3 | 4 | 5 | 6 | 7 |
| 2. I examine the bottoms of my feet             | 0                                     | 1 | 2 | 3 | 4 | 5 | 6 | 7 |
| 3. I examine between the toes of my feet        | 0                                     | 1 | 2 | 3 | 4 | 5 | 6 | 7 |
| 4. I wash my feet                               | 0                                     | 1 | 2 | 3 | 4 | 5 | 6 | 7 |
| 5. I wash between my toes                       | 0                                     | 1 | 2 | 3 | 4 | 5 | 6 | 7 |
| 6. I dry my feet after washing it               | 0                                     | 1 | 2 | 3 | 4 | 5 | 6 | 7 |
| 7. I dry between my toes after washing my feet. | 0                                     | 1 | 2 | 3 | 4 | 5 | 6 | 7 |

Section 2: Below is a list of activities your may have to perform to manage your feet. Please read each one and then circle the category which best reflects what you actually do. For example, if you are always carry out that you are able to protect your feet, circle 7. If you feel that sometimes you could do it, circle 4 or 3. If you feel that all of the time you never do it, circle 0.

|                                                                                                 | Never | sometimes |   |   |   |   |   | Always |
|-------------------------------------------------------------------------------------------------|-------|-----------|---|---|---|---|---|--------|
| 8. I trim my toenails straight across.                                                          | 0     | 1         | 2 | 3 | 4 | 5 | 6 | 7      |
| 9. I apply moisturizing lotion to my feet.                                                      | 0     | 1         | 2 | 3 | 4 | 5 | 6 | 7      |
| 10. I wear cotton and loose socks every time I walk (includes walking indoors).                 | 0     | 1         | 2 | 3 | 4 | 5 | 6 | 7      |
| 11. I wear suitable (wide) shoes/ sturdy slippers every time I walk (includes walking indoors). | 0     | 1         | 2 | 3 | 4 | 5 | 6 | 7      |
| 12. Before I put on my shoes/ sturdy slippers, I check the inside of my shoes/ sturdy slippers. | 0     | 1         | 2 | 3 | 4 | 5 | 6 | 7      |
| 13. I break in new shoes/ sturdy slippers slowly                                                | 0     | 1         | 2 | 3 | 4 | 5 | 6 | 7      |
| 14. I choose suitable and correct shoes/ sturdy slippers for my feet.                           | 0     | 1         | 2 | 3 | 4 | 5 | 6 | 7      |
| 15. I tell my doctor/ nurse/ medical assistant (if any) about problems with my feet             | 0     | 1         | 2 | 3 | 4 | 5 | 6 | 7      |
| 16. I recognize when my toenails need to be trimmed by a doctor/ nurse/ medical assistant       | 0     | 1         | 2 | 3 | 4 | 5 | 6 | 7      |

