### **1.6.1 Foot self-care behaviour**

In this study, foot self-care behaviour will be rate on the number of days (for one week) patients perform a certain behaviour such as examine the bottoms of feet and between the toes, wash and dry between toes, apply moisturizing lotion to feet, nail care, check the inside of the shoes and break in new shoes slowly (Chin & Huang, 2013).

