This evaluation is the last phase, where health provider and elderly with diabetes will determine the goals is achieved or not. The primary outcomes is the foot self-care behaviour will be improved, the foot self-care behaviour worse, or there is no significant difference of foot self-care behaviour before and after implementation phase. The secondary outcome are level of foot care efficacy expectation, foot care outcome expectation, knowledge on foot care and quality of life. During this phase the effectiveness of the program will be assessed through the questionnaire form of quality of life, knowledge on foot care, foot care efficacy expectation, foot care outcome expectation and foot self-care behaviour.

[figure not shown]

Figure 2.3 The conceptual framework for development and evaluation self-efficacy enhancing program on foot self-care behaviour of elderly with diabetes

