## 3.6 Instruments

### 3.6.1 Questionnaire

The questionnaire will be prepared in English and Malay language. Respondents need to answer the questionnaire independently if they were able to read and write. Interview will be conducted only for those illiterate respondents. The information that will gathered to answer objectives of the study the respondents are as follow;

Section A is demographic data. The information required are about age, ethnicity, gender, education level, marital status, number of children, frequency of being visited by children/ relatives and friends and duration of stay in RSK.

Section B is clinical characteristics. The data will gather about FBS level, duration of diabetes, treatment of diabetes, other disease (except diabetes), smoking status, hospitalization due to diabetes problem and previous diabetes education received.

Section C measure on foot self-care behaviour. The Diabetes Foot Self-Care Behaviour Scale (DFSBS) (Chin & Huang, 2013) will be adapted in this study. The DFSBS contains 16 items. The scale had two parts: In the first part, the responses will be rated on the number of days patients performed a certain behaviour over the course of one week (0 for never, 7 for every day they performed the activity). In the second part, the responses will rated by the frequency with which patients performed a certain behaviour in general, from never (0) to always (5). The responses will be rated as a 5-point Likert scale [never/ 0 day per week (1), rarely/ 1-2 days per week (2), sometimes/ 3-4 days per week (3), often/ 5-6 days per week (4) and always/ 7 days per week (5)] (Chin & Huang, 2013). A higher score indicated good foot self-care behaviour.

Section D is measure on foot care self-efficacy (foot care efficacy expectation). The Foot Care Confidence Scale (FCCS) (Sloan, 1998) will be adapted to this study. The instrument is a public domain. There are 12 items measuring on self-confidence in managing foot care. The scale given into five scores; strongly not confident (score 1) to strongly confident (5). Higher scores shows high in self-confidence in managing foot care behaviour.

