## Part D: Foot care self-efficacy (efficacy expectation)

After reading each statement, please tick ( ✓ ) under the description that best describes how CONFIDENT you are about undertaking yourself each of the following foot-care tasks. Please answer **about your CONFIDENCE to do the foot care, not about what you actually do.**

|                                                                                                                          | Strongly
not
confident |  |  | Strongly
confident |
|--------------------------------------------------------------------------------------------------------------------------|------------------------------|--|--|-----------------------|
| 1. I can protect my feet                                                                                                 |                              |  |  |                       |
| 2. Even without pain/discomfort, I can look at my feet daily to check for cuts, scratches, blisters, redness or dryness. |                              |  |  |                       |
| 3. After washing my feet, I can dry between my toes.                                                                     |                              |  |  |                       |
| 4. I can judge when my toenails need to be trimmed by a podiatrist                                                       |                              |  |  |                       |
| 5. I can trim my toenails straight across                                                                                |                              |  |  |                       |
| 6. I can figure out when to use a pumice stone to smooth corns and/or calluses on my feet.                               |                              |  |  |                       |
| 7. I can test the temperature of the water before putting my feet into it.                                               |                              |  |  |                       |
| 8. If I was told to do so, I can wear shoes and socks every time I walk (includes walking indoor).                       |                              |  |  |                       |
| 9. When I go shopping for new shoes, I can choose shoes that are good for my feet.                                       |                              |  |  |                       |

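### The Part C Section 2 instruction, which governs 9 of the 16 primary-outcome items, asks for actual behaviour but then illustrates the scores partly in terms of ability

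*Combined protocol and SAP*

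**What the plan says.** Section 2.6 sets the outcome hierarchy: "The primary outcomes is the foot self-care behaviour will be improved". Efficacy expectation is listed there as a secondary outcome.

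Two places define the primary outcome as something performed. Section 1.6.1 says that "foot self-care behaviour will be rate on the number of days (for one week) patients perform a certain behaviour". Section 3.6.1 says of the second part of the scale that "the responses will rated by the frequency with which patients performed a certain behaviour in general".

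The form itself is in the appendix questionnaire, Part C. The Section 2 instruction starts in line with those definitions: "Please read each one and then circle the category which best reflects what you actually do". Three worked examples follow:

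- Score 7: always carrying out the activity, run together with being able to protect one's feet.
- Scores 3 or 4: "If you feel that sometimes you could do it, circle 4 or 3".
- Score 0: never doing it.

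Part D, the confidence scale, draws the line between the two constructs explicitly. It asks residents to answer "about your CONFIDENCE to do the foot care, not about what you actually do".

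**The concern.** Feeling that one could do a task is efficacy expectation, not behaviour. The middle example asks for the former and the top example blends the two, directly after a sentence that asks for the latter. A resident who follows the examples rather than the lead sentence would score perceived ability on those items.

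This matters more here than in most trials because the programme is built to raise self-efficacy (section 3.7.1 and Table 3.3) while controls receive usual care. If felt ability rises more in the intervention arm, and some residents score by the examples, part of that rise could be recorded as behaviour. The primary outcome and a secondary outcome would then overlap. Stored scores could not separate the two meanings afterwards, because a circled 4 looks the same whichever was intended.

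**Working it through.** **Share of the scale affected.** The plan states that "The DFSBS contains 16 items". On the form, Section 1 holds items 1 to 7 and Section 2 holds items 8 to 16, so 7 + 9 = 16 and the plan's count is reproduced.

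- Items: 9/16 = 56.25%.
- Points on the printed 0 to 7 format: 9 × 7 = 63 of 16 × 7 = 112, again 56.25%.
- Range on the 1 to 5 scoring in section 3.6.1: 9 × 4 = 36 of 16 × 4 = 64, again 56.25%.

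The share does not depend on which scoring is used. It is the share of the scale under the contradictory instruction, not an estimate of bias.

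**What each part of Section 2 asks for.**

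| Element | Construct |
|---|---|
| Lead sentence | Behaviour |
| Column heads (never, sometimes, always) | Frequency |
| Items 8 to 15 | First-person actions |
| Item 16 | Recognising a need; not plainly an action |
| Example for 7 | Doing mixed with ability |
| Example for 3 or 4 | Ability |
| Example for 0 | Behaviour |

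The conflict is confined to the examples: one of three is worded wholly as ability and a second partly so.

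**How close Section 2 lies to Part D.** Eight of the nine items have a near counterpart on the confidence scale:

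- item 8 (cutting nails straight) with D5
- item 9 (lotion) with D12
- items 10 and 11 (socks and footwear when walking) with D8
- item 12 (looking inside shoes) with D11
- item 14 (choosing shoes) with D9
- item 15 (reporting problems) with D10
- item 16 (nails needing professional care) with D4

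Only item 13 has none. The ability clause in the score-7 example also resembles D1, while no Section 2 item asks about protecting the feet in general. With content this similar, the framing as doing or being able is the main thing that separates the two scales.

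**Would a planned step catch it?**

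- Cronbach's alpha (sections 3.6.2.1 and 3.6.2.2) measures internal consistency. It would not show that respondents answered about ability.
- The factor analysis in section 3.9 names only the FCCS and FCOE, not the DFSBS.
- Forward and back translation (section 3.6.2.1) checks fidelity to the English, so it would tend to carry the wording over.
- The pilot (section 3.6.2.2) looks for ambiguous words and instructions, and six content experts comment on the draft (section 3.7.1). Either might catch it; neither is directed at it.

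**The case against.** The strongest reply is that the form is behavioural wherever it counts. The governing sentence asks for what is done, the column heads are frequencies, and the items are nearly all first-person actions. The top example begins with carrying the activity out. In unpolished draft English, the middle example may simply mean sometimes managing to do it. All of that stands, and it is why the effect may be near zero.

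A reader might infer that the form tells residents to score what they feel able to do. It does not: the lead sentence says the opposite, and only the example for scores 3 and 4 is worded wholly as ability.

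A reader might also infer that any distortion falls on the intervention arm alone. The documents do not support that either. Both arms complete the same form at baseline, week 4 and week 12. A false effect would need felt ability to change differently between arms without a matching change in behaviour, among residents who let the examples override the rest of the form. The bias could even run the other way. Entrants must be independent in daily activities (section 3.5.3), so many may already feel capable. An ability reading would then raise baseline scores in both arms and compress a real difference.

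Finally, it is tempting to express a shift on nine items as a fraction of the 3.90-point difference in section 3.5.2. That difference comes from a different study. Nothing in the plan shows that the study used the DFSBS, and no figure says how far the wording would move any answer. Such a ratio would not be evidence of size.

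The expert review and pilot also stand as a partial answer, because the form is still a draft. They do not guarantee a correction, since neither is pointed at these sentences.

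**Conclusion.** The Section 2 instruction is internally inconsistent. It conflicts with the definitions in sections 1.6.1 and 3.6.1 and blurs the line that Part D draws. It covers 9 of 16 primary-outcome items, 56% of the scale.

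Leakage of perceived ability into the behaviour score is a risk, not something the documents show. It rests on the assumption that some residents answer by the examples; that share is unknown and may be zero. A differential effect needs the further assumption that felt ability changes differently between arms, which is plausible given the programme's aim but not established. Size and direction are unknown.

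The Malay wording of Part C is not in the text available to me, so I cannot say whether the problem carries over. The sample size is unaffected. This is a drafting fault in the primary instrument, worth correcting because it is cheap now and cannot be repaired from the stored scores later.

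**What to change.** Before translation and before the pilot at RSK Cheras, replace the three Section 2 examples with frequency-of-doing wording, for instance: *If you always do it, circle [top score]; if you sometimes do it, circle [middle score]; if you never do it, circle 0.* Delete the clause about being able to protect the feet and the clause about what one could do. The placeholders are deliberate: the form prints 0 to 7 and section 3.6.1 describes other ranges, so the numbers should follow whichever format is settled.

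Use the same wording in the Malay form and whenever the form is read aloud to residents who cannot read. The latter matters because the researcher who interviews them also knows the allocation (sections 1.7 and 3.3). In the pilot, ask a few respondents whether they answered Section 2 about what they do or what they feel able to do.

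The cost is a few reworded sentences and one or two extra questions in the pilot interview already planned in section 3.6.2.2. No participants, visits or analyses change.

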## Part D: Foot care self-efficacy (efficacy expectation)

After reading each statement, please tick ( ✓ ) under the description that best describes how CONFIDENT you are about undertaking yourself each of the following foot-care tasks. Please answer **about your CONFIDENCE to do the foot care, not about what you actually do.**

|                                                                                                                          | Strongly
not
confident |  |  | Strongly
confident |
|--------------------------------------------------------------------------------------------------------------------------|------------------------------|--|--|-----------------------|
| 1. I can protect my feet                                                                                                 |                              |  |  |                       |
| 2. Even without pain/discomfort, I can look at my feet daily to check for cuts, scratches, blisters, redness or dryness. |                              |  |  |                       |
| 3. After washing my feet, I can dry between my toes.                                                                     |                              |  |  |                       |
| 4. I can judge when my toenails need to be trimmed by a podiatrist                                                       |                              |  |  |                       |
| 5. I can trim my toenails straight across                                                                                |                              |  |  |                       |
| 6. I can figure out when to use a pumice stone to smooth corns and/or calluses on my feet.                               |                              |  |  |                       |
| 7. I can test the temperature of the water before putting my feet into it.                                               |                              |  |  |                       |
| 8. If I was told to do so, I can wear shoes and socks every time I walk (includes walking indoor).                       |                              |  |  |                       |
| 9. When I go shopping for new shoes, I can choose shoes that are good for my feet.                                       |                              |  |  |                       |
| 10. I can call my doctor about problems with my feet .                                                                   |                              |  |  |                       |
| 11. Before putting them on, I can check the insides of my shoes for problems that could harm my feet.                    |                              |  |  |                       |
| 12. If I directed to do so, I can routinely apply lotion to my feet.                                                     |                              |  |  |                       |

